### Fecal microbiome processing, sequencing, bioinformatics, and statistical analysis

4.1

Fecal collection kits and detailed instructions will be provided to participants. Samples will be stored at −80 °C until processing. DNA will be extracted using the PowerSoil Pro DNA kit (Qiagen). For short-read profiling, the V4–V5 region of the 16S rRNA gene will be amplified using primers 515F and 926R with Illumina barcodes. For long-read profiling, the 16S-ITS-23S operon will be amplified with primers A515F and U2428R and PacBio barcodes to obtain amplicons > 3,500 bp. Sequencing of both short- and long-read libraries will be performed by the Sequencing Core at the University of Illinois at Urbana-Champaign (UIUC). Raw sequence data will be processed in the R statistical environment; DADA2, a bioinformatics pipeline, specifically developed for modeling and correcting amplicon sequencing errors (Callahan et al., 2016), will be used for quality assessment, length filtering, denoising high-quality reads into Amplicon Sequence Variants (ASVs) and chimera removal.

Given the complexity of the dataset, microbiome statistical analysis will be conducted using standardized and reproducible methodologies. α- and β-diversity analyses will be assessed at appropriate taxonomic levels, from phylum to genus, using the phyloseq package in R (McMurdie and Holmes, 2013). α-diversity will be estimated using indices such as Shannon, Simpson, and Faith’s phylogenetic diversity and between-group differences will be tested using appropriate non-parametric test (e.g., Kruskal-Wallis) for cross-sectional comparisons or generalized linear models adjusted for covariates. For longitudinal analyses across T0, T1, FU1, and FU2, mixed-effects models will be used where appropriate to account for repeated measures within participants. β-diversity will be quantified using distance metrics including Bray-Curtis, Jaccard, and weighted/unweighted Unifrac. The prespecified primary microbiome analysis will focus on Bray–Curtis β-diversity and will evaluate whether the change from T0 to T1 differs between the combined intervention (Group C) and standard care (Group D) using Permutational Multivariate Analysis of Variance (PERMANOVA). To account for the repeated-measures structure, permutation testing will be restricted within participants. FU1 and FU2 will be included in secondary/exploratory analyses of durability/maintenance.

To evaluate the effect of sequencing platform and interindividual variability, (PERMANOVA) will be applied. Concordance between PacBio and Illumina community profiles will be assessed using Mantel and Procrustes tests and reported as exploratory. Taxonomic composition will be analyzed using complementary approaches such as ANCOM-BC (as primary compositional method) and DESeq2, LEfSe as exploratory approaches, to identify taxa or pathotypes showing significant differences between experimental groups. Multiple-testing correction will be applied (e.g., Benjamini–Hochberg) where applicable. Data will be appropriately normalized and, if necessary, transformed. Dimension-reduction techniques, including principal component analysis (PCA), principal coordinates analysis (PCoA) or non-metric multidimensional scaling (NMDS), will be used to visualize sample clustering and compositional differences.

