### Participants and eligibility criteria

3.2

The calculation of the sample size was not strictly required given the pilot nature of this study. Accordingly, the target sample size was primarily driven by feasibility considerations and the need to obtain precise effect-size estimates to inform a definitive RCT. However, to support the microbiome endpoint, we performed an *a priori* power assessment. Following the recommendations of Ferdous et al. (2022), we selected β-diversity as the primary endpoint to detect differences between groups in the composition of intestinal microbial species. Using G*Power version 3.1.9.7, assuming an effect size of (Cohen’s f) 0.25, a statistical power of 0.95 (1−β) and setting α to 0.05, we estimated the minimum required sample size. To account for expected attrition during the intervention and follow-up period (approximately 10%), the total sample size was increased to 80 participants (20 per arms). Participants will be recruited from Clinical Trial Centers for Parkinson’s Disease (RU1 - RU2) during routine clinical visits. A total of eighty (*n* = 80) participants meeting the following eligible criteria will be enrolled and randomly assigned to an intervention or to the control group:

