#### Primary outcome

3.5.1

The primary endpoint of the PRIME study is to evaluate the effect of the interventions on GM β-diversity in PD patients, defined as the change in Bray-Curtis dissimilarity from T0 (baseline) to T1 (end of intervention). The prespecified primary contrast will be the between-group difference in the T0-T1 change in β-diversity for the combined intervention (Group C) versus standard care (Group D). As supportive primary microbiome descriptors, we will also quantify α-diversity and taxonomic composition/relative abundance, with analyses primarily intended to describe community structure and to support interpretation of β-diversity findings. Microbiome profiling will be performed using third-generation, high-resolution long-read sequencing technology, the Pacific Biosciences (PacBio) system, capable of sequencing amplicons up to ∼20,000 base pairs (bp) (Biada et al., 2025; Buetas et al., 2024). Exploratory microbiome aims will include (i) identification of stage-associated microbial patterns and candidate non-invasive microbiome biomarkers, treated as hypothesis-generating, and (ii) a methodological comparison between PacBio long-read sequencing and Illumina MiSeq short-read 16S rRNA amplicon sequencing. The comparison will evaluate relative performance in terms of taxonomic resolution and community profiling, with particular attention to the ability of PacBio to achieve higher resolution at the species level. We will also assess the degree of compositional similarity between microbial communities characterized by the two platforms, thereby determining the feasibility and potential benefits of integrating sequences from different technologies in microbiome research. FU1 and FU2 assessments will be used for exploratory analyses of the durability/maintenance of microbiome changes beyond the end of the intervention. Results from these exploratory analyses will be interpreted in the context of the pilot design.

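### The primary β-diversity endpoint is stated for species composition, but section 4.1 limits β-diversity analysis to ranks from phylum to genus and does not say which rank carries the primary test

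*Protocol article*

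**What the plan says.** Four statements in the protocol article bear on the level of the primary endpoint.

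- **Purpose (section 3.2).** The article explains its choice in these words: "we selected β-diversity as the primary endpoint to detect differences between groups in the composition of intestinal microbial species".
- **Platform (section 3.5.1).** "Microbiome profiling will be performed using third-generation, high-resolution long-read sequencing technology", namely PacBio. The exploratory comparison with Illumina is to be made "with particular attention to the ability of PacBio to achieve higher resolution at the species level". The Introduction also names the limited taxonomic resolution of short reads as one of the gaps that PRIME addresses.
- **Feature unit (section 4.1).** DADA2 is used for steps that include "denoising high-quality reads into Amplicon Sequence Variants (ASVs) and chimera removal". ASVs are finer than genus.
- **Analysis range (section 4.1).** α- and β-diversity "will be assessed at appropriate taxonomic levels, from phylum to genus, using the phyloseq package in R".

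Most of the primary test is fixed in sections 3.5.1 and 4.1: Bray-Curtis, change from T0 to T1, Group C versus Group D, PERMANOVA. Section 4 sets the threshold for the primary analysis at 0.05 and reserves false-discovery-rate control for exploratory high-dimensional analyses. No section states the taxonomic level at which the primary Bray-Curtis matrix is built.

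**The concern.** The range in section 4.1 covers β-diversity as a whole, and the primary-analysis sentence later in that section does not exempt itself. Followed literally, the only prespecified primary test runs at genus or coarser, while its stated aim is to find differences in species composition.

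Two things are at stake. First, replacement of one species by another within a genus leaves the genus total unchanged, so the primary test could miss part of what it was chosen to find. Second, the range spans several ranks with no rule for choosing among them. Each rank gives its own distance matrix and its own p-value, and each could be presented as the primary result.

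**Working it through.** **1. The plan's own figure.** The only figure attached to this endpoint is the sample size in section 3.2: f = 0.25, power 0.95, α = 0.05, about 10% attrition, total 80. The G*Power test family, number of measures and correlation are not given, so these inputs alone do not determine N. The closest variant found assumes a repeated-measures within-between ANOVA with 4 groups, 2 time points and correlation 0.5:

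- Noncentrality = f² × N × m / (1 − ρ) = 0.0625 × 72 × 2 / 0.5 = 18, with 3 and 68 degrees of freedom.
- Power at 72 completers = 0.948, and 72 / 0.9 = 80.
- A strict solve for power of at least 0.95 in multiples of 4 gives 76, which inflates to 85.

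The figure is therefore approached but not reproduced. What matters here is that no taxonomic rank enters the calculation, so naming a rank does not change N.

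**2. The texts side by side.**

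| Element | Section | Level |
|---|---|---|
| Purpose of the primary endpoint | 3.2 | species |
| Unit produced by denoising | 4.1 | ASV |
| β-diversity analysis | 4.1 | phylum to genus |
| Primary PERMANOVA | 4.1 | none stated, no exception to the range |

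The first and third rows cannot both govern the primary test.

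**3. What aggregation hides.** On relative abundances, Bray-Curtis is half the sum of absolute differences. Let a share δ move from one species to another in the same genus, with all else unchanged.

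- Species level: (δ + δ) / 2 = δ.
- Genus level: the two changes cancel, giving 0, and likewise at every coarser rank.

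Shifts that do not cancel within a genus remain visible at genus level.

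**4. Number of candidate tests.** Phylum to genus covers five standard ranks: phylum, class, order, family, genus. If the smallest of five p-values were reported at 0.05:

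- fully correlated tests: 5%
- independent tests: 1 − 0.95^5 = 1 − 0.774 = 22.6%

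The ranks are nested sums of the same reads. Their p-values are correlated, though not perfectly, so the figure lies between these two.

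**5. Illustration on synthetic data (an assumption, not trial data).** The set-up was 200 species nested in 80 genera, 35 families, 18 orders, 10 classes and 6 phyla, with log-normal abundances. There were 18 participants per group (20 less 10%), and two groups were compared at one time point by PERMANOVA on Bray-Curtis.

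- No true difference, 600 data sets: at least one of the five ranks from genus to phylum rejected in 10.7%. The Monte Carlo standard error is √(0.107 × 0.893 / 600) = 1.3 percentage points.
- Opposing shifts that partly cancel within genera, 300 data sets: rejection was 99.7% at species, 82% at genus, 73% at family, 65% at order, 36% at class and 32% at phylum.

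The second set was built to show cancellation. It shows that the rank can change the result, not by how much it would do so in PRIME.

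**The case against.** The strongest objection is that a condensed article commonly leaves the primary rank to the full protocol or statistical analysis plan, neither of which is shown. Silence on the rank would indeed be no finding. But the article is not silent: it states a range, and the range excludes the level it gives for the endpoint. A later plan that names species departs from section 4.1, and one that names genus departs from section 3.2.

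It can also be said that the word species in section 3.2 is loose language for members of the community, and that genus is a defensible primary level because finer tables are sparse. Both are possible. Neither removes the mismatch, but they are reasons to leave the final choice of level to the sponsor.

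A reader might infer more than the text supports:

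- **That the trial was powered on species.** The effect size of 0.25 is generic. Only the purpose of the endpoint is stated at species level.
- **That the species-resolution wording in section 3.5.1 defines the primary endpoint.** It belongs to the exploratory platform comparison, although PacBio is also the profiling platform.
- **That species composition is never tested, or that its signal is wholly lost.** The range applies to diversity analyses. The differential-abundance methods described later in section 4.1 carry no rank limit.
- **That listing Faith's index and UniFrac contradicts the range.** Both can be computed on a tree merged to genus, and neither is the primary metric.
- **That the false-positive rate is 23%.** That needs five independent tests and selection of the best. Nested ranks cannot be independent, and the article does not say that a rank will be picked after results are seen.

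Blinding of the bioinformatics analysts (section 3.4.1) reduces the scope for selection but does not name the rank.

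**Conclusion.** The point holds as a contradiction in the text about the sole primary test. The endpoint is stated for species composition, and the range set for β-diversity stops at genus. Metric, time window, contrast and test are fixed; the rank is the one element examined here that is open, with five candidates.

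The size depends on what is done. With one rank named in advance, the error stays at 5%. With the best of five chosen after results, it lies above 5% and below the 22.6% independence bound; the synthetic example gave about 11%. The sensitivity lost by working at genus or above cannot be quantified from the documents, since it depends on how far the interventions move species within genera. The conclusion does not rest on the sample-size figure or on the synthetic example. It should be settled before the primary analysis, because this is the only confirmatory test in a pilot meant to inform a definitive trial.

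**What to change.** Reconcile sections 3.2, 3.5.1 and 4.1:

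1. In section 4.1, extend the range of levels for diversity analysis down to species or ASV.
2. Name one level, in advance, for the primary Bray-Curtis PERMANOVA of Group C versus Group D on PacBio data. Species or ASV matches the stated purpose.
3. Make genus the single sensitivity analysis, because finer tables are sparser, and label the remaining ranks descriptive.
4. If the sponsor prefers genus as primary, reword section 3.2 so that it claims genus-level composition only.

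This costs one or two sentences, written before anyone sees results by group. It needs no new data, no change to sequencing and no change to the sample size. The price of a species or ASV primary is a sparser table, which the genus-level sensitivity analysis covers.

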### Monitoring

4.2

Because the trial objectives and a short follow-up period, monitoring responsibilities will rest with the study protocol team and the local Institutional Review Board (IRB); no independent Data Monitoring Committee (DMC) will be established. Study data will be accessible only to authorized and trained staff via unique, password-protected accounts; electronic data will be stored on secure servers with appropriate technical safeguards.

## Discussion

5

The aging global population will likely produce a rising incidence of Parkinson’s disease (PD) with attendant social and economic burdens. Although pharmacological treatment has advanced, no durable disease-modifying therapy is currently available, underscoring the need to investigate accessible, cost-effective non-pharmacological strategies. The PRIME study addresses this gap by evaluating the synergistic effects of combined nutritional and physical-activity interventions on the GM and on both motor and non-motor clinical outcomes. By adopting a factorial design, the trial can disentangle the effects of each intervention alone and in combination, thereby providing robust comparative data. Clarifying the temporal and potentially causal relationships between gut microbiome alterations and PD — and how these relationships respond to diet and exercise — may facilitate the identification of an easily accessible, non-invasive stage specific biomarker for PD, a need that is unmet at present. The study’s findings are expected to inform future non-pharmacological protocols, including multidisciplinary rehabilitation programs, aimed at slowing disease progression, reducing symptom burden, and enabling earlier diagnosis. When implemented through well-structured rehabilitation pathways, these interventions are anticipated to improve patients’ independence and quality of life, and to result in fewer hospital admissions and lower long-term care costs. These outcomes will have immediate translational potential for clinical practice and meaningful benefits for health-care systems.
